**(2) Baseline/treatment period (D1):**

**【Inclusion/Exclusion Criteria】** : For subjects who met the enrollment criteria, the investigators informed the subjects of the treatment tooth position information.

**【Vital signs】** : respiration, heart rate, blood pressure (systolic and diastolic), temperature (axillary), and clinical assessment of general condition.

**【Periodontal Clinical Indicators】** : Periodontal examination was standardized using the Florida Probe of the Beijing Stomatological Hospital, Capital Medical University. Records: periodontal attachment level AL, periodontal probing depth PD, probing bleeding index BOP, gingival recession GR, tooth mobility TM, and the proposed treatment site (single tooth/subject) were selected by the investigator.

**【Lab Tests】** :

☞ Blood routine: leukocytes, erythrocytes, hemoglobin, erythrocyte pressure product, mean erythrocyte volume, mean hemoglobin volume, mean hemoglobin concentration, platelet count, mean platelet volume, platelet pressure product, neutrophils, lymphocytes, monocytes, eosinophils, basophils, neutrophil absolute value, lymphocyte absolute value, monocyte absolute value, eosinophil absolute value, basophil absolute value, erythrocyte distribution width SD, erythrocyte distribution width CV, large platelet ratio, platelet distribution width.

☞ Hemorrhagic and coagulation function: plasma prothrombin time, international normalized ratio of prothrombin time, activated partial thromboplastin time, prothrombin time, plasma fibrinogen.

☞ Liver and kidney function: alanine aminotransferase, aspartate aminotransferase, total protein, albumin, globulin, albumin-globulin ratio, total bilirubin, direct bilirubin, indirect bilirubin, alkaline phosphatase, creatinine,  $\gamma$ -glutamine acyltransferase, lactate dehydrogenase, creatine kinase, urea, uric acid, total carbon dioxide, glucose.

☞ Inflammatory markers: ultrasensitive C-reactive protein.

☞ Infectious disease tests: HBsAg, HBsAb, HBeAg, HBeAb, HBcAb, Anti-HCV, HIVcombin, Anti-TP, CMV-IgM, CMV-IgG.

☞ Immunologic tests: IgA, IgG, IgM, total IgE.

☞ Pregnancy test: blood beta-HCG, premenopausal female subjects only.

☞ Urine routine: pH, specific gravity, protein, ketone bodies, bilirubin, urobilinogen, nitrites, leukocytes, erythrocytes, urine sugar, urine sediment microscopy.

**【Basic periodontal treatment】** : All groups of subjects underwent ultrasonic supragingival cleaning, subgingival scraping of half of the mouth and root planing. Periodontal irritants such as plaque were removed. Periodontal basic treatment required the preservation of residual dentin on the root surface according to basic principles. The investigators recorded the start and end times of the subjects' periodontal basic treatments.

■ Supragingival cleaning (D-1, included therapeutic tooth area): 2% Articaine Hydrochloride anesthesia, half-mouth ultrasonic subgingival scaling, root planning, polishing and physiological saline rinse.

**【Local injection treatment】** : The investigator, according to the randomized assignment number, were treated with periodontal basic therapy and perform bilateral multi-point inject DPSCs/saline injection immediately after the completion of periodontal basic therapy. The injection method was as follows: under local anesthesia, a periodontal probe was used to determine the position of the top of the alveolar ridge, and the needle was inserted into the bottom of the periodontal pocket (in the tissue around the bottom of the periodontal pocket). After the needle reaches the periodontium on the inner side of the alveolar ridge and touches

the junction of bone surface and root, a 1 ml screw-port syringe was used for buccal (labial), lingual (palate) injection with the inject time of 20-30 seconds per point. Stopping point of the injection needle is located on the root surface to ensure that the drug can be concentrated in the root area.

■ DPSCs injection group: a single treatment dose of 0.6 mL / tooth, cell volume of about  $1 \times 10^7$  hDP-MSC cells / tooth / person, suspension of saline 0.6 mL / tooth.

■ Saline injection group: a single treatment dose of 0.6 mL /tooth.

The investigator recorded the start and end time of the subjects' local injection treatments.

**【Vital signs】** : Checked 2h±30min after the end of local injection treatment. Record: respiration, heart rate, blood pressure (systolic, diastolic), temperature (axillary), and clinical assessment of general condition.

**【Laboratory tests】** : 2h±30min after the end of local injection treatment.

☞ Inflammation index: ultrasensitive C-reactive protein.

☞ Immunologic tests: IgA, IgG, IgM, total IgE.

**【Record of adverse events】** : All subjects in all groups were observed for 2 hours after treatment and left the hospital, during which adverse reactions were recorded.

**【Record of combined medication/treatment】**

**【Intraoral photography】** : Photographs were taken to record the condition of the oral cavity and treatment sites.

**(3) Post-treatment follow-up 1:** Telephone follow-up 1 week (D7±1 day) after the end of treatment.

**【Adverse event record】**

**【Record of combined medication/treatment】**

**(4) Post-treatment follow-up visit 2:** One month (D30±3 days) after the end of treatment.

**【Vital signs】** : respiration, heart rate, blood pressure (systolic and diastolic), temperature (axillary), and clinical assessment of general condition.

**【Lab Tests】** :

☞ Blood routine: leukocytes, erythrocytes, hemoglobin, erythrocyte pressure product, mean erythrocyte volume, mean hemoglobin volume, mean hemoglobin concentration, platelet count, mean platelet volume, platelet pressure product, neutrophils, lymphocytes, monocytes, eosinophils, basophils, neutrophil absolute value, lymphocyte absolute value, monocyte absolute value, eosinophil absolute value, basophil absolute value, erythrocyte distribution width SD, erythrocyte distribution width CV, large platelet ratio, platelet distribution width.

☞ Hemorrhagic and coagulation function: plasma prothrombin time, international normalized ratio of prothrombin time, activated partial thromboplastin time, prothrombin time, plasma fibrinogen.

☞ Liver and kidney function: alanine aminotransferase, aspartate aminotransferase, total protein, albumin, globulin, albumin-globulin ratio, total bilirubin, direct bilirubin, indirect bilirubin, alkaline phosphatase, creatinine,  $\gamma$ -glutamine acyltransferase, lactate dehydrogenase, creatine kinase, urea, uric acid, total carbon dioxide, glucose.

☞ Inflammatory markers: ultrasensitive C-reactive protein.

☞ Infectious disease tests: HBsAg, HBsAb, HBeAg, HBeAb, HBcAb, Anti-HCV, HIVcombin, Anti-TP, CMV-IgM, CMV-IgG.

☞ Immunologic tests: IgA, IgG, IgM, total IgE.

☞ Pregnancy test: blood beta-HCG, premenopausal female subjects only.

☞ Inflammation indicator: ultrasensitive C-reactive protein, only for subjects in the double DPSCs injection group of Phase II of this study

**【Adverse Event Record】**

**【Record of combined medications/treatments】**

**【Double DPSCs Injection Treatment】** : only for subjects in the double DPSCs injection group in Phase II of this study. At the end of the one-month follow-up visit, subjects received a bilateral multi-point inject hDP-MSC. Periodontal defect sites were injected in the same manner as the first local injection treatment.

■ Double DPSCs injection group: at the end of the one-month follow-up visit, the subjects were given bilateral multipoint injections into individual tooth sites at a single treatment dose of about  $1 \times 10^7$  hDP-MSC (saline 0.6mL suspension) / tooth / person.

The investigators recorded the start and end time of the subjects' local injection treatments.

**【Vital Signs】** :only for subjects in the Phase II double DPSCs injection group of this study. 2h±30min after the end of local injection treatment, record: respiration, heart rate, blood pressure (systolic and diastolic), temperature (axillary), and clinical assessment of general condition.

**【Laboratory tests】** :Only for subjects in the Phase II S double DPSCs injection group of this study. After the local injection treatment 2h±30min after the end of local injection treatment.

☞Inflammation indicator: Ultrasensitive C-reactive protein.

☞Immunologic tests: IgA, IgG, IgM, total IgE.

**【Adverse event record】** : Only for subjects in the Phase II Stem Cell Secondary Dosing Group of this study, who were observed 2 hours after treatment before left the hospital and adverse events were record.

(5) **Post-treatment follow-up 3:** 3 months (D90±3 days) after the end of treatment.

**【Periodontal Clinical Indicators】** : Periodontal examination was standardized using the Florida Probe of the Beijing Stomatological Hospital, Capital Medical University. Records: periodontal attachment level AL, periodontal probing depth PD, probing bleeding index BOP, gingival recession GR, tooth mobility TM, and the proposed treatment site (single tooth/subject) were selected by the investigator.

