| Research procedure | 
(1) Screening for inclusion (D-14) : After the subjects signed the informed consent, all pre-enrollment screening examinations were conducted in the periodontal/emergency comprehensive clinic of the research institution. Subjects who met the inclusion criteria and did not meet the exclusion criteria were selected Join the group. The investigator selected the subject's proposed treatment site (single tooth position/subject).
 
(2)Periodontal primary treatment (D-14~D1) : Periodontal primary treatment includes supragingival scaling, subgingival scaling and root treatment The surface is flat. Divided into 3 times, the specific treatment steps are as follows:
 
 
■ Supragingival cleaning (D- 14) : normal saline rinse and gargle, whole mouth ultrasonic supragingival cleaning and polishing, normal saline rinse;
 
■ Subgingival scaling (D-7±1, non-therapeutic dental area) : 2% bilan anesthesia, half-mouth ultrasonic subgingival scaling, flat root surface, polishing, normal saline rinse;
 
■ Subgingival scaling (D1, including treatment area) : 2% bilan anesthesia, the other half of the mouth ultrasound subgingival scaling, root surface flat, polishing, normal saline rinse.
 
 
(3) Local injection therapy (D1) : According to the randomly assigned number, all subjects were given bilateral multi-point local injection therapy of hDP-MSC cells/normal saline immediately after the peridental foundation treatment was completed. The local injection method for the peridental defect site is: Under local anesthesia, the periodontal probe was used to determine the top position of the alveolar ridge, and the needle was injected into the bottom of the periodontal bag (in the surrounding tissue at the bottom of the periodontal bag). After the needle reached the medial periodontal membrane of the alveolar ridge and touched the junction between the bone surface and the tooth root, the multi-point interstitial injection was performed on both sides of the buccal (lip) and lingual and palatine sides with a 1ml spiral syringe. The injection time is 20-30 seconds at each point. The stop point of the injection needle is located on the tooth root surface to ensure that the injected stem cell preparation can be in the tooth root The area is clustered. Specific operations are as follows:
 
 
■ DPSCs injection group: 48 subjects. Immediately after the completion of periodontal basic treatment, the patient was given bilateral multi-point injection at a single dental position, and the therapeutic dose was <math>1 \times 10^7</math> hDP-MSC cells (0.6mL suspension of normal saline)/dental position/person.
 
■ Saline iniecton group: 48 subjects. Immediately after the completion of periodontal basic treatment, the patient was given bilateral multi-point injection at a single dental position, and the therapeutic dose was 0.6mL normal saline/dental position/person.
 
 
Local stem cell secondary injection therapy (D30±3) : Only for secondary stem cells in the second phase of this study Subjects in the administration group. At the end of a one-month follow-up, the subjects were given more hDP-MSC cells on both sides Point local injection therapy. The local injection method of periodontal defect site is the same as the first local injection treatment:
 
 
■ Double DPSCs iniecton group: After 1 month follow-up, the subjects received bilateral multi-point injection at a single dental position and the therapeutic dose It was <math>1 \times 10^7</math> HDP-MSC cells (saline 0.6mL suspension)/dental position/person.
 
 
(4) Observation (D1) : After treatment, all subjects were admitted to the periodontal/emergency comprehensive clinic 2 Hours of adverse reactions observation and safety assessment.
 
(5) Follow-up (D7±1 telephone follow-up, D30±3, D90±3, D180±5, D360±5) :
 
 
■ Post-treatment follow-up: Subjects were followed up at D7±1 (telephone follow-up), D30±3, D90±3, and D180±5 once each after discharge, and clinical safety and efficacy indexes were collected.
 
■ Long-term follow-up: After the end of treatment, D360±5 follow-up was conducted once, clinical efficacy and immunological evaluation indicators were collected, and the study was ended.
 
 |

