|  | 
During the screening period, before treatment, 2h±30min after the end of treatment, D30±3 during the follow-up period, and 2h±30min after the end of treatment in the second phase of stem cell secondary administration group in this study.
 
②Laboratory tests
 
 
● Routine blood count: white blood cells, red blood cells, hemoglobin, hematocrit, mean corpuscular volume, mean hemoglobin amount, mean hemoglobin concentration, platelet count, mean platelet volume, thrombocrit, neutrophils, lymphocytes, monocytes, eosinophils, basophils, neutrophils absolute, lymphocyte absolute, monocyte absolute, eosinophil absolute, basophil absolute, erythrocyte distribution width SD, erythrocyte distribution width CV, large platelet ratio, platelet fraction cloth width; During the screening period, before treatment, and during the follow-up period, D30±3, D90±3, D180±5 were examined.
 
● Coagulation: plasma prothrombin time, international normalized ratio of prothrombin time, activated partial thromboplastin time, plasma prothrombin time, plasma fibrinogen; at screening and before treatment.
 
● Liver and renal function: alanine aminotransferase, aspartate aminotransferase, total protein, albumin, globulin, white globule ratio, total bilirubin, direct bilirubin, indirect bilirubin, alkaline phosphatase, creatinine, gamma-glutamyltransferase, lactate dehydrogenase, creatine kinase, urea, uric acid, total carbon dioxide, glucose; D30±3, D90±3, and D180±5 at Screening, Pre-treatment, and Follow-up Periods.
 
● Inflammatory indicators: ultrasensitive C-reactive protein, examined during the screening period, before treatment, 2h±30min after the end of treatment, the and subjects in the secondary stem cell dosing group in the second phase of this study before, at the end of the secondary dosing treatment 2h±30min after
 
● Infectious disease testing: HBsAg 、HBsAb 、HBeAg 、HBeAb 、HBcAb 、Anti-HCV 、HIVcombin 、Anti-TP 、CMV-IgM 、CMV-IgG; During the screening period and follow-up period, D30±3, D90±3, D180±5 were examined.
 
● Immunological tests: IgA, IgG, IgM, total IgE; examined during the screening period, pre-treatment, 2h±30min after the end of treatment, D30±5, D90±5, D180±5, D360±5 during the follow-up period and 2h±30min after the end of the secondary administration of treatment for subjects in the secondary administration group of the second phase of the present study of stem cells.
 
● Pregnancy test: blood β-HCG, D30±5, D90±5, D180±5 in premenopausal female subjects during screening, pre-treatment, and follow-up periods.
 
● Urine routine: pH, specific gravity, protein, ketone bodies, bilirubin, urobilinogen, nitrite, leukocytes, erythrocytes, urine glucose, urine urine urine test. cells, erythrocytes, urine glucose, urine sediment microscopy, in the screening period, before treatment.
 
 
For subjects with adverse reactions, timely treatment, follow-up inspection and recording should be carried out in accordance with the diagnosis and treatment routine.
 
③Adverse events and serious adverse events: The occurrence of adverse events and serious adverse events was recorded in a timely manner during the study, and the degree of adverse events was determined according to the NCI CTCAE v4.03 grading standard. Swollen and painful gums within one week after surgery will be recorded as an adverse event and judged by the investigator to be a treatment-related adverse reaction.
 |

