In phase II, there were 3 groups and 50 subjects. After the subjects with a clinical diagnosis of chronic moderate periodontitis signed an informed consent form and met the inclusion criteria while did not meet the exclusion criteria, the investigator randomly assigned them to saline injection group, approximately 30 subjects; Single DPSCs injection group, approximately 10 subjects; Double DPSCs injection group, approximately 10 subjects, based on the randomization grouping codes provided by the statistician. The randomization envelopes were collected by the Numerical Statistics Unit upon completion of this phase. The investigator selected the proposed treatment sites for the subjects (individual tooth site/subject). All subjects were treated with periodontal basic therapy and perform bilateral multi-point inject hDP-MSC/saline immediately after the completion of periodontal basic therapy. At the end of the one-month follow-up, double DPSCs injection group received a bilateral multi-point inject hDP-MSC/saline.

In summary, the two phases of this study, saline group is expected to enroll approximately 33 subjects, single DPSCs injection group is expected to enroll approximately 33 subjects, and double DPSCs injection group is expected to enroll 30 subjects, which meets the requirements of statistical analysis.

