The laboratory tests included in the safety assessment indicators of this study will be carried out by the laboratory department. Some of the test items will require blood samples to be sent to an external testing facility for examination. These items include high-sensitivity C-reactive protein, infectious disease testing (cytomegalovirus CMV-IgM, cytomegalovirus CMV-IgG), immunological testing (IgA, IgG, IgM, total IgE), and pregnancy tests. The testing will be conducted after a trilateral agreement is signed between the research institution, the preparation institution, and the external testing facility. The external testing facility is Beijing Edicon Medical Laboratory Co., Ltd., which has obtained ISO 15189 accreditation, CMA metrology certification, and CLIA certification from the CAP, known as the "gold standard" for clinical laboratories. After the completion of the external blood sample testing for this study, Beijing Edicon Medical Laboratory Co., Ltd. will be responsible for the uniform destruction of the samples and will provide periodic destruction certificates to the research institution.

The imaging tests included in the efficacy assessment indicators of this study will be conducted using CBCT measurement, which will be carried out by the radiology department.

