  - Immunology: IgA, IgG, IgM, Total IgE; During the screening period, before administration, 2h±30min after the end of administration, D30±5, D90±5, D180±5, D360±5, and the second dose group of stem cells in the second stage of this study 2h ±30min after the end of the second dose treatment.
  - Pregnancy test: blood β-HCG, premenopausal female subjects in the screening period, pre-drug, follow-up period D30±5, D90±5, D180±5 inspection.
  - Urine routine: PH value, specific gravity, protein, ketone body, bilirubin, urobilinogen, nitrite, white blood cells, red blood cells, urine glucose, urine sediment microscopic examination, during the screening period, before treatment.
- (3) For subjects with adverse reactions, timely treatment, follow-up inspection and recording should be carried out in accordance with the diagnosis and treatment routine.
- (4) Adverse events and serious adverse events: The occurrence of adverse events and serious adverse events was recorded in a timely manner during the study, and the degree of adverse events was determined according to the NCI CTCAE v4.03 grading standard. Swollen and painful gums within one week after surgery, recorded as an adverse event, judged by the investigator to be an administration-related adverse reaction.

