- Blood count: leukocytes, erythrocytes, hemoglobin, erythrocyte pressure volume, mean erythrocyte volume, mean hemoglobin concentration, platelet count, mean platelet volume, platelet pressure, neutrophil, lymphocytes, monocytes, eosinophils, basophils, absolute value of neutrophils, absolute value of lymphocytes, absolute value of monocytes, absolute value of eosinophils, absolute value of basophils, erythrocyte distribution width SD, erythrocyte distribution width CV, large platelet ratio, platelet distribution width.
- Liver and kidney function: alanine aminotransferase, aspartate aminotransferase, total protein, albumin, globulin, white globule ratio, total bilirubin, direct bilirubin, indirect bilirubin, alkaline phosphatase, creatinine, gamma-glutamyltransferase, lactate dehydrogenase, creatine kinase, urea enzyme, lactate dehydrogenase, creatine kinase, urea, uric acid, total carbon dioxide, glucose.
- Infectious disease detection: HBsAg, HBsAb, HBeAg, HBeAb, HBcAb, Anti-HCV, HIVcombin, Anti-TP, CMV-IgM, CMV-IgG.
- Immunological tests: IgA, IgG, IgM, Toal IgE.
- Pregnancy test: blood beta-HCG, for premenopausal female subjects only.
- Inflammatory indicators: only for subjects in the secondary stem cell dosing group in phase II of this study before secondary dosing treatment, examined  $2h \pm 30min$  after the end of treatment.

c. Record of adverse events

d. Record of combined medications/treatments

e. Intraoral photography: photographic record of oral cavity and treatment site conditions.

**3. Post-treatment follow-up 3:** conducted 3 months ( $D90 \pm 3$  days) after the end of treatment.

a. Periodontal Clinical Indicators: Periodontal Clinical Indicators: Periodontal examinations were standardized using the Florida Probe of the Beijing Stomatological Hospital of Capital Medical University. Records: periodontal attachment level AL, periodontal probing depth PD, probing bleeding index BOP, gingival recession GR, and tooth looseness TM.

b. Laboratory tests:

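### The second injection in the double arm does not have to wait for the visit 2 pregnancy test result

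*Protocol*

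**What the plan says.** Section (V), Study steps, item (4), describes visit 2. Its laboratory list includes "Pregnancy test: blood beta-HCG, premenopausal female subjects only". The treatment paragraph for the double arm then reads "At the end of the one-month follow-up visit, subjects received a bilateral multi-point inject hDP-MSC". Section (V), item 2.5, gives the same order: "At the end of the one-month follow-up, double DPSCs injection group received a bilateral multi-point inject hDP-MSC/saline". The scenario summary (Research procedure) places this injection at D30±3. The schedule of assessments shows the pregnancy test and the second injection in the same D30±3 column.

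Section (XX), item 2, repeats the visit 2 test: "Pregnancy test: blood beta-HCG, for premenopausal female subjects only". Two other places state its timing differently. The scenario summary (Safety Assessment) has "Pregnancy test: blood β-HCG, D30±5, D90±5, D180±5 in premenopausal female subjects during screening, pre-treatment, and follow-up periods", and section (15), item 1, has "premenopausal female subjects in the screening period, pre-drug, follow-up period D30±5, D90±5, D180±5 inspection".

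Section (6), item 2, lists the samples that leave the hospital: "These items include high-sensitivity C-reactive protein, infectious disease testing (cytomegalovirus CMV-IgM, cytomegalovirus CMV-IgG), immunological testing (IgA, IgG, IgM, total IgE), and pregnancy tests". It gives no turnaround time.

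Pregnancy during the study is a withdrawal criterion (section (V), item 2.4; section (7), item 3). Section (16), item 10, requires immediate discontinuation and acknowledges possible effects on the woman and the fetus.

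**The concern.** A drawn sample protects nobody until its result has been read. The test and the dose share one visit, the test is run off site, and no sentence links the two. The withdrawal and discontinuation rules apply only once a pregnancy is known; they do not detect one before dosing.

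Of the three follow-up pregnancy tests (D30, D90, D180), only the one at D30 can precede a dose. It is therefore the only one that can prevent an exposure rather than record it. At stake is a second exposure to an allogeneic cell product during an undetected pregnancy, which the protocol itself treats as a possible risk.

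**Working it through.** No formula or stated figure is involved. The check sets the relevant provisions side by side and does the day counts.

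**First dose against second dose**

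| Safeguard | First injection (D1) | Second injection (D30±3) |
|---|---|---|
| Earlier pregnancy test | Screening beta-HCG, plus a D1 sample | D1 sample, plus a sample at visit 2 itself |
| Eligibility check | Screening and D1 (schedule; section (9), item 5) | None scheduled |
| Rule that a negative result precedes the dose | Pregnancy is an exclusion criterion, re-checked at D1 | None |

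**Gap since the last sample before visit 2.** The D1 sample precedes the second injection by 27 − 1 = 26 days at the earliest, 30 − 1 = 29 days nominally, and 33 − 1 = 32 days at the latest. A conception in those days can be found only by the visit 2 test or through another route, such as the woman's own report.

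**Whether the visit 2 sample can stop the dose.** Section (13), item 1, has product ordered one day ahead. Section (6), item 2, limits storage to 10 hours after preparation. Product made for that visit can therefore be held for a late result by less than 10 hours, since transport and release testing use part of that time. The turnaround is not given, so both cases have to be shown:

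- Result back within hours: the dose can be withheld.
- Result back after a day or more: the dose has been given, or has expired, before the result is known.

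**Whether another sentence closes the gap.** The pre-drug time point in section (15), item 1, might be taken to cover both doses. The same line lists D30 separately as follow-up. Where the authors meant the second dose they named it: C-reactive protein is required before and after it, and vital signs and immunoglobulins after it (scenario summary; section (15), item 1). Beta-HCG has no such link.

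**Number of women.** The scenario summary and section (8) plan 30 subjects in the double arm, with no restriction by sex. One sentence in section (V), item 2.5, says about 10, but the summary paragraph that follows it returns to 30, so 30 is used as the upper bound. The number of premenopausal women is not stated.

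**The case against.** The strongest case on the other side is that most of the protection is already there. A D30 test is scheduled and comes before the injection. Pregnancy leads to withdrawal and immediate discontinuation. Exclusions (11) to (13) bar recent unprotected sex, pregnancy, and plans to become pregnant. A pregnancy known from any source, including the woman herself, stops dosing. The turnaround may also be fixed in the separate three-party laboratory agreement mentioned in section (6), item 2, which is not at hand.

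Much of this stands. It makes the affected group small and leaves open whether results in practice arrive in time. It does not supply the missing condition. The exclusions lower the chance of pregnancy, yet the protocol still tests at D30, D90 and D180, so it does not treat that chance as nil. Whether a dose is safe to give should not depend on an unstated laboratory interval.

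A reader might go further and infer from the ±5 days in the scenario summary and section (15) that the protocol allows the test after the injection, for example at D35. The documents do not support that. The test belongs to visit 2, which is D30±3 in the schedule and in section (XX), and the injection closes that visit. The ±5 conflicts with the visit windows, and does so again at D90, where the visit is ±3. It is better read as an inconsistency than as permission for a late draw. Nor should a reader infer that a woman known to be pregnant could be injected again; the withdrawal rules prevent that.

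**Conclusion.** The point holds as a narrow safety gap. The sample precedes the second dose, but no text requires its result first and no eligibility check is scheduled at D30. A woman who conceived after D1 can be re-injected under the protocol as written, unless the result returns within hours or the pregnancy is already known by another route.

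The size is bounded by the premenopausal women among the 30 subjects planned for the double arm, and within them by those who conceive between D1 and the injection without knowing it. The expected number cannot be calculated from the documents and is likely to be small. No efficacy conclusion is affected. The conclusion assumes that visit 2 is carried out in the order described and that pregnancy tests go to the outside laboratory as section (6) says. It is still worth correcting, because the test is already planned and only its link to the dose is missing.

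**What to change.** In the scenario summary (Research procedure, secondary injection), section (V) Study steps (4), and section (XX) item 2, state for premenopausal women in the double group:

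1. A negative pregnancy test result must be on file before the second injection. It may come from blood beta-HCG drawn a few days before the injection or from a same-day rapid test at the site.
2. Before injecting, the investigator confirms that no withdrawal criterion in section (7), item 3, is met.

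Add the same condition as a footnote to the pregnancy-test and drug-delivery rows of the schedule. In the scenario summary (Safety Assessment) and section (15), item 1, replace D30±5 for this test in this group with a requirement that it be done before the second injection with the result available.

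**Cost.** An early draw may add one trip per premenopausal woman, at the 300 RMB per visit in section (9), item 7. The ceiling is 30 × 300 = 9,000 RMB if every subject in the arm were such a woman. It also leaves uncovered the days between draw and injection; for example, a draw on D27 for a D30 injection leaves 30 − 27 = 3 days. A same-day rapid test removes both the trip and those days, but it adds a simple test that the protocol does not now include. With either route, a positive result may occasionally leave a prepared dose unused, because product is ordered one day ahead and keeps for at most 10 hours. Section (13), item 4, already provides for recovering unused product.
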